### Secondary outcomes

Specific details regarding all the secondary outcomes can be found in the statistical analysis plan in online supplementary appendix 7. The secondary outcomes will include:
The change in chest pain VAS scores from randomisation to 12 months postrandomisation between the study arms;The change in quality of life (as measured by EQ5D and QLQ-C30) from randomisation to 12 months postrandomisation between the study arms;The difference in analgaesia requirements between the study arms;The difference in the size, symptom severity and time to development of PTM between the study arms;The rate and severity of radiotherapy toxicity;The number of serious adverse events (SAEs) related to radiotherapy or a PTM;The health economic implications of immediate and deferred radiotherapy;The identification of emergent themes from the semistructured interviews.

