## Methods and analysis

The surgical and large bore procedures in malignant pleural mesothelioma and radiotherapy trial (SMART Trial) is a multicentre, prospective, RCT. The trial is sponsored by North Bristol NHS Trust and coordinated by The Respiratory Research Unit at North Bristol NHS Trust. Data management is undertaken by the Oxford Respiratory Trials Unit. The trial is registered on the International Standardised Randomised Controlled Trial Registry (ISRCTN72767336) and funded by the National Institute for Health Research (NIHR), Research for Patient Benefit (RfPB) Programme. The study is included in the NIHR Clinical Research Network portfolio (ID: 11023). The trial will be conducted in accordance with the Declaration of Helsinki and Good Clinical Practice (GCP).

The primary research question is to evaluate whether prophylactic radiotherapy prevents PTM following large bore pleural procedure in MPM.

The secondary research questions are:

In MPM:
Does prophylactic radiotherapy lead to differences in patient symptoms and quality of life indices as compared to radiotherapy given in the event a PTM develops?What proportion of PTM are symptomatic (ie, painful) and to what extent is this modulated by giving prophylactic radiotherapy?In a subgroup of patients with IPCs, is prophylactic radiotherapy effective in reducing PTM?Does prophylactic radiotherapy cause toxicity and impact on the quality of life of patients?Is deferred radiotherapy (given when a nodule develops) as effective as prophylactic radiotherapy at controlling symptoms?What is the patient experience of immediate and deferred radiotherapy?What are the health economic implications of giving prophylactic radiotherapy as compared to deferred radiotherapy in this patient group?

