### Sample size calculation

The sample size calculation was based on internal audit data showing a PTM rate of <2% in those treated with prophylactic radiotherapy who underwent ‘large’ bore procedures, in comparison to a rate of between 8% and 40% in the published literature of patients not undergoing prophylactic radiotherapy.

Assuming the rates of PTM to be 2% in the intervention group and 15% in the ‘control’ group, 180 patients are required to demonstrate a difference between treatment arms with 90% power at the 5% significance level. With an estimated lost to follow-up rate of 3%, this number is increased to 185 patients randomised 1:1. Various power modelling scenarios were considered (see table 1), demonstrating adequate power with varied control and intervention event rates if 203 patients are recruited.

**Table 1 BMJOPEN2014006673TB1:** Sample size calculations for different predicted PTM rates

	Control group As needed radiotherapy					
Intervention group Prophylactic radiotherapy	90% power (α 0.05, 3% loss to FU)			80% power (α 0.05, 3% loss to FU)		
Incidence of PTM at 12 months (%)	12	15	18	12	15	18
1	203	150	118	153	112	88
2	269	185	140	201	140	105
3	357	234	169	266	174	125
4	482	294	203	360	220	152
5	670	375	248	500	281	184

All rates include a projected 3% loss to follow-up. The figures in the shaded cells are those which are achievable within the proposed sample size.

FU, follow up; PTM, procedure tract metastasis.

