### Statistical analysis plan

The full statistical analysis plan can be viewed in online supplementary appendix 7. The analysis will be based on intention-to-treat principles.

For continuous outcomes, analyses will adjust for the minimisation factors and the outcome measured at baseline (provided there is no substantial missing baseline data). For binary outcomes, if the number of events allows, the analysis will adjust for the minimisation factors. If major baseline imbalances between the treatment arms are identified, these may also be adjusted for in the regression models.

For missing baseline data, if the numbers are small, median imputation will be used. If the numbers with missing data are large, alternative analysis methods may be used, which do not account for baseline values.

CONSORT data will be presented including the number of patients screened for the study and the numbers randomised. Reasons for exclusions after randomisation will be given.

Analysis for all outcomes will be presented as:
The number of participants included in the analysis, by treatment group;A summary statistic for the outcome, by treatment group (eg, mean (SD) or median (2.5th–97.5th centile) for continuous outcomes; number (%) for binary outcomes);A treatment effect, with a 95% CI and p value (2 sided; the significance level set at 5%).

The primary outcome, incidence of PTM within 12 months, will be analysed on an intention-to-treat basis. The proportion of patients developing a PTM (as defined above) within 12 months from randomisation or until death or loss to follow-up (whichever is sooner) will be calculated for both trial arms and compared using Fisher’s exact test. Alternatively, if the number of events allows, logistic regression will be performed, adjusting for the minimisation variables and any substantial baseline imbalances.

A secondary, per protocol analysis will be performed for the primary outcome, excluding patients with major protocol violations.

If numbers allow, the following subgroup analyses will be performed for the primary outcomes:
By the type of pleural intervention randomised (large bore chest drain, local anaesthetic thoracoscopy, IPC or thoracic surgery);By tumour subtype (epithelioid only or other);Patients who were alive and in trial follow-up for at least 6 months (yes/no);Patients who received chemotherapy for mesothelioma within 12 months from trial entry (yes/no).

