### End of the trial

The trial will end once 203 patients have been recruited and all patients have died or completed 1 year of trial follow-up (whichever is sooner).

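### PTM size, symptom severity and the painful share of PTM are to be compared between arms within a subset that the treatment itself selects

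*Protocol article*

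**What the plan says.** Four statements in the protocol article bear on this.

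- **Secondary outcomes:** one item is "The difference in the size, symptom severity and time to development of PTM between the study arms". The section refers to the statistical analysis plan (appendix 7, not shown) for details.
- **Methods and analysis, secondary research questions:** "What proportion of PTM are symptomatic (ie, painful) and to what extent is this modulated by giving prophylactic radiotherapy". The denominator is PTMs, not patients.
- **Primary outcome:** the authors prefer a comparison of proportions because they expect radiotherapy to prevent PTMs rather than alter how fast they appear.
- **Statistical analysis plan:** every outcome is to be presented with "A treatment effect, with a 95% CI and p value (2 sided; the significance level set at 5" per cent). The same section bases the analysis on intention to treat. It makes no exception for PTM size or severity and does not call them descriptive.

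**The concern.** Whether a patient has a PTM is determined after randomisation, and changing it is the purpose of the treatment. PTMs in the immediate arm are those that broke through radiotherapy. PTMs in the deferred arm are all those that arose without it. A difference in mean size, or in the share that are painful, mixes any effect on a given nodule with the effect on which nodules appear at all. An analysis restricted to cases is not an intention-to-treat comparison, whatever label it carries.

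The Introduction motivates the trial by the pain that PTMs can cause, so whether radiotherapy reduces painful PTM is a central question for patients. The painful share of PTMs can rise while the number of patients with a painful PTM falls. A p value attached to that share would invite the wrong conclusion.

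**Working it through.** **1. Inputs** (Sample size calculation; End of the trial)
- Rates and size: "Assuming the rates of PTM to be 2% in the intervention group and 15% in the ‘control’ group, 180 patients are required"; this is "to demonstrate a difference between treatment arms with 90% power at the 5% significance level".
- Loss: "With an estimated lost to follow-up rate of 3%, this number is increased to 185 patients randomised 1:1".
- Recruitment: "The trial will end once 203 patients have been recruited".

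**2. The plan's own figure.** Two proportions, two-sided 5%, 90% power, unpooled variance:
- n per arm = (1.960 + 1.282)² × (0.02×0.98 + 0.15×0.85) / (0.15 − 0.02)² = 10.51 × 0.1471 / 0.0169 = 91.5, so 92 per arm and 184 in total, against 180 stated (within 3%).
- From the stated 180, 180/0.97 = 185.6, against 185 stated.

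The design rates are therefore read as the authors used them.

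**3. Expected PTM cases.** 203 × 0.97 = 196.9, taken as 98 immediate and 99 deferred.

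| Rates (immediate / deferred) | Immediate cases | Deferred cases | Chance of no immediate-arm case |
|---|---|---|---|
| 2% / 15% (design) | 98×0.02 = 1.96 | 99×0.15 = 14.85 | 0.98⁹⁸ = 14% |
| 1% / 12% (Table 1) | 98×0.01 = 0.98 | 99×0.12 = 11.88 | 0.99⁹⁸ = 37% |
| 4% / 18% (Table 1) | 98×0.04 = 3.92 | 99×0.18 = 17.82 | 0.96⁹⁸ = 2% |

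At the design rates the immediate arm has at most two cases with probability 69%. Without the 3% loss the design counts are 101.5×0.02 = 2.0 and 101.5×0.15 = 15.2.

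**4. Precision if exactly 2 and 15 cases occur.** For a two-sample t-test on size, the noncentrality is d/√(1/2 + 1/15) with 15 degrees of freedom. Power is 24% for a difference of 1 SD, and 80% power needs about 2.3 SD. For painful yes/no, Fisher's test gives p = 0.044 at 2/2 v 2/15 and p = 0.074 at 2/2 v 3/15.

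**5. Direction: painful share.** Suppose 1 of 2 PTMs is painful in the immediate arm and 6 of 15 in the deferred arm (a hypothetical split).
- Among cases: 1/2 = 50% v 6/15 = 40%, so radiotherapy looks worse.
- Per patient: 1/98 = 1% v 6/99 = 6%, so radiotherapy looks better.

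**6. Direction: size.** Assume lognormal nodule sizes (median 2 cm, log SD 0.5, ignoring the 1 cm threshold), and that radiotherapy changes no nodule's size but lets only 0.02/0.15 = 13% through. The deferred-arm mean is 2×e^0.125 = 2.3 cm. The immediate-arm mean depends on which nodules escape:
- chance of escape proportional to size: 2×e^0.375 = 2.9 cm;
- inversely proportional to size: 2×e^(−0.125) = 1.8 cm;
- unrelated to size: 2.3 cm.

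Selection alone can therefore produce a difference in either direction, or none. The sizes are assumptions; the documents give none.

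**The case against.** **The analysis plan is not shown.** It may already treat size and severity as descriptive, and severity could be defined over all patients. That is possible. But the article itself puts PTMs in the denominator of the pain question, asks how radiotherapy modulates the result, and promises an effect and p value for every outcome. Those statements would still have to be aligned with such a plan. The first half of the research question, what share of PTMs are symptomatic, is a legitimate descriptive aim.

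**The contrast would not be read alone.** PTM incidence is compared in all randomised patients, and chest pain and analgesic use are separate outcomes that do not require a PTM. This stands and limits the harm. None of these outcomes, however, is painful PTM per randomised patient.

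**The counts of 2 and 15 depend on the design rates.** This also stands. In the earlier trials described in the Introduction, PTM rates (radiotherapy v control) were 7% v 10% and 23% v 10%. Applied per patient here, these give 98×0.07 = 6.9 v 99×0.10 = 9.9 cases, and 98×0.23 = 22.5 v 9.9. The immediate arm would not then be nearly empty. Selection is a concern whenever radiotherapy changes who develops a PTM, and the second pair is far from equal.

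**Two wider readings that the article does not support.**
- A reader might infer that time to PTM is also compared among cases only. The Primary outcome section plans time-to-event regression as a secondary analysis and does not restrict it to cases; such models ordinarily include everyone.
- A reader might infer that "The change in chest pain VAS scores from randomisation to 12 months postrandomisation between the study arms", and the matching quality-of-life outcome, rest on 12-month survivors alone. Nothing says so. Questionnaires are collected at 1, 3, 6, 9 and 12 months and pain scores in the months between, and how they are modelled is left to the analysis plan.

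**Conclusion.** The point holds for PTM size, PTM symptom severity and the painful proportion of PTM. As the article words them, these are between-arm effects, with p values, in a group defined by an event the treatment is expected to prevent. They cannot be read as effects of radiotherapy. At the design rates they would rest on about 2 cases against 15, with a 14% chance that the immediate arm contributes none. The counts are expectations that depend on those rates; the selection problem requires only that radiotherapy affects who develops a PTM. The painful split and the nodule sizes in the illustrations are assumed.

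The point does not extend to time to PTM, or to the 12-month chest pain and quality-of-life outcomes. The primary analysis is untouched. What is at risk is one secondary conclusion, though on a question that matters to patients.

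**What to change.** - Make painful PTM within 12 months of randomisation (yes/no) the between-arm outcome, over all randomised patients, with patients without a PTM counted as no. Follow-up to death or loss can be handled as in the primary outcome. State what counts as painful, using the symptom data already recorded.
- Report PTM size and symptom severity among cases by arm as description, with numbers of cases and without a between-arm p value. Say that these groups are selected after randomisation.
- Reword the research question so that the share of PTMs that are symptomatic is descriptive and the effect of radiotherapy is asked per randomised patient. Exempt the descriptive items from the rule that every outcome gets an effect and p value.
- Check the analysis plan and align it.

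The cost is wording in the protocol and analysis plan. No new data are needed. The article reports the trial as still in follow-up, so the change can be made before the analysis.

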### Randomisation

Following informed consent, patients will be randomly assigned (1:1) to receive either immediate prophylactic radiotherapy (within 42 days of the pleural intervention) or deferred radiotherapy (given if the patient develops a PTM).

Treatment allocation will be performed over the telephone by UKCRC Oxford Respiratory Trials Unit. The randomisation sequence will be generated using a validated, online randomisation service (Sealed Envelope, London, UK; http://www.sealedenvelope.com). Minimisation with a random component will be used to reduce the baseline between-group differences.

The minimisation factors are:
Histological tissue type of mesothelioma (epithelioid only or other);IPC or other pleural procedure;Surgical procedure (ie, open pleural biopsy, thoracotomy or VATS) or non-surgical procedure.

Patients and clinicians will not be blinded to treatment allocation; however, the data analysis will be conducted in a blinded fashion.

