### Safety reporting

Data will be collected at each trial visit regarding any SAEs (as defined by GCP). All SAEs causally related to radiotherapy or a PTM will be reported to the sponsor and followed until they resolve or stabilise.

Radiotherapy toxicities will be recorded at each follow-up visit (according to the Radiation Therapy Oncology Group (RTOG) grading system).

IPC complications will also be recorded at each clinic visit.

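### The SAE outcome is limited to events judged related to radiotherapy or a PTM in an open-label trial; all SAEs by arm should be shown beside it, with the two causes split

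*Protocol article*

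**What the plan says.** The protocol article's Secondary outcomes section has two items on harm. One is "The rate and severity of radiotherapy toxicity"; the next is "The number of serious adverse events (SAEs) related to radiotherapy or a PTM". No item covers SAEs regardless of cause. Four other items in the list say that the arms are compared; the SAE item does not. However, the Statistical analysis plan section states that all outcomes will be presented by treatment group with a treatment effect, 95% CI and two-sided p value, so the SAE count falls under that rule.

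On blinding, the Randomisation section says: "Patients and clinicians will not be blinded to treatment allocation; however, the data analysis will be conducted in a blinded fashion".

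The Safety reporting section separates collection from reporting. Collection is unrestricted: "Data will be collected at each trial visit regarding any SAEs (as defined by GCP"). The restriction by cause applies to onward reporting and follow-up: "All SAEs causally related to radiotherapy or a PTM will be reported to the sponsor and followed until they resolve or stabilise". Toxicity has its own record: "Radiotherapy toxicities will be recorded at each follow-up visit (according to the Radiation Therapy Oncology Group (RTOG) grading system"). The article does not say who judges causality, and it leaves the details of the secondary outcomes to an analysis plan in an appendix that is not shown.

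**The concern.** An SAE enters this outcome only after someone has judged its cause. Two things can then go wrong in an arm comparison.

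- **Attribution.** Which label an event can receive depends on what happened after randomisation. A radiotherapy label needs radiotherapy; a PTM label needs a PTM. Any tendency to over-use or under-use a label acts unequally on the arms. Blinding the analyst does not help, because the label is already in the data. A serious harm of radiotherapy that is put down to mesothelioma is not counted at all.
- **Combination.** A single count adds harm of the treatment to harm of the event that the treatment is meant to prevent. These are expected mainly in opposite arms, so a null difference in the sum need not mean that radiotherapy did no serious harm.

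At stake is one of the trial's stated secondary questions: whether prophylactic radiotherapy causes toxicity.

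**Working it through.** The article gives no SAE rate, attribution rate or SAE power, so there is no figure of the plan's own to reproduce. What can be worked out is how the definition behaves.

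**Inputs**
- PTM rate 2% immediate and 15% deferred (Sample size calculation). The same section gives 8% to 40% as the published range without prophylaxis.
- Protocol radiotherapy: planned for everyone in the immediate arm; in the deferred arm only after a PTM (Interventions).
- About 101 patients per arm (203 randomised 1:1).

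**Step 1: who can receive the radiotherapy label.** At 15%, about 101 × 0.15 = 15 deferred patients receive protocol radiotherapy. The exposure ratio is 1/0.15 = 6.7. Over the published range it runs from 1/0.40 = 2.5 to 1/0.08 = 12.5. By itself this is the randomised contrast, not a bias.

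**Step 2: effect of mislabelling.** Assume no true harm and the same all-cause SAE risk in both arms. Let r be the chance that an SAE in an irradiated patient is wrongly labelled radiotherapy-related, and p the chance that an SAE in a patient with a PTM is wrongly labelled PTM-related (overlap ignored). The fractions of SAEs counted are:
- immediate: r + 0.02p
- deferred: 0.15r + 0.15p

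With k = p/r, the ratio of immediate to deferred is (1 + 0.02k) / (0.15(1 + k)). For assumed values of k:
- k = 0: 1/0.15 = 6.7
- k = 1: 1.02/0.30 = 3.4
- k = 6.5: 1.13/1.125 = 1.0
- k = 10: 1.20/1.65 = 0.73

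The ratio is 1 only where 0.85r = 0.13p, so p = 6.5r. If the deferred PTM rate is 8% instead, balance needs 0.92r = 0.06p (p = 15.3r); at 40% it needs 0.60r = 0.38p (p = 1.6r). The distortion can therefore favour either arm. It vanishes if no event is mislabelled or if the overall labelled fraction happens to be equal in both arms.

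**Step 3: cancellation with every label correct.** Let h be the true risk of a radiotherapy-caused SAE per irradiated patient, and g the true risk of a PTM-caused SAE per patient with a PTM. The expected values are h + 0.02g and 0.15h + 0.15g. The algebra is the same: if g is about 6.5h, the arms show equal counts although radiotherapy causes serious harm. The article gives neither h nor g.

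**Step 4: precision of an all-cause comparison.** With assumed SAE risks of 30% and 40% and 101 per arm, SE = √(0.30×0.70/101 + 0.40×0.60/101) = √(0.45/101) = 0.067. The 95% half-width is 1.96 × 0.067 = 0.13, or about 13 points. Power for that 10-point excess is about 32% (0.10/0.0667 = 1.50; 1.50 − 1.96 = −0.46).

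**The case against.** The strongest counter-case has four parts.

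- **Harm is measured elsewhere.** RTOG-graded toxicity is a separate outcome aimed directly at the toxicity question, and chest pain, quality of life and analgesic use are compared between arms without any causal judgement. This stands: a reader might infer that related SAEs are the trial's only safety outcome, and they are not. But the toxicity record also depends on recognising a harm as due to radiotherapy, so it does not catch serious harm ascribed to the disease.
- **Bias is not shown.** A reader might infer that the comparison is biased by its very construction. The article does not support that. Unequal exposure is the treatment contrast, the definition covers consequences of both strategies, and distortion needs mislabelling or cancellation. A calculation on the radiotherapy label alone, such as 30% SAE risk × 10% labelled × exposure, giving 3.0% v 0.45%, rests on assumed rates and leaves out PTM-related events, which fall mainly in the deferred arm. It does not show what this outcome would yield.
- **The assessor is not named, and details sit in the analysis plan.** Both are true. That an unblinded clinician judges causality is a reasonable inference from the Randomisation section, not a stated fact. The analysis plan may already split the causes or tabulate all SAEs, and silence on that in the article is no fault. The restriction itself, however, is stated in the article.
- **All-cause SAEs are noisy.** In a fatal disease they may be mostly disease events, and Step 4 shows limited power. This stands, and it argues against replacing the related count. It does not argue against adding a table.

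The pooled count can also be defended as a net burden of two strategies. It is then an answer to a different question from whether radiotherapy causes toxicity.

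**Conclusion.** The point holds as a cheap improvement. As stated, the SAE outcome rests an arm comparison on a causal label whose availability depends on allocation, in a trial where clinicians are unblinded, and it adds treatment harm to harm from the event being prevented. It is open to attribution bias and hard to interpret when pooled.

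The only size that the article supports is the difference in exposure to protocol radiotherapy: about 6.7 to 1 at the planned 15% PTM rate, or 2.5 to 12.5 over the published range. That figure takes nearly all immediate-arm patients as irradiated and ignores radiotherapy for other indications, which the Standard care section allows. The size and direction of any bias in the SAE count cannot be derived, because no SAE or attribution rate is given. The primary analysis and the sample size are unaffected.

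**What to change.** Keep the related count and add to it:

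1. All SAEs by randomised arm, whatever the attribution: patients with at least one SAE and number of events, with the difference and 95% CI.
2. Radiotherapy-related and PTM-related SAEs as two separate rows instead of one combined figure.

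If the analysis plan already does this, a sentence in the Secondary outcomes section is enough.

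The cost is one extra table from data that the Safety reporting section says are collected anyway. The downside is imprecision: disease-related SAEs will dilute the all-cause comparison (about ±13 points on the assumed rates above), so a null result there should not be read as evidence of no harm.
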